### Statistical procedures

#### Continuous outcomes (axial length, spherical equivalent change)

For outcomes measured on a continuous scale (i.e., axial length growth and change in spherical equivalent), we will use analysis of variance (ANOVA) or linear regression models. In these models, the subgroup classifications (based on device usage and near work duration) will be the main independent variables. Adjustments will be made for covariates such as age, gender, baseline refractive error, and outdoor activity time to control for potential confounding. Model selection will follow a strategy to achieve parsimony—incorporating only those covariates that are theoretically justified and empirically significant.

#### Binary outcomes (myopia incidence and proportion of fast progressors)

For binary outcomes, logistic regression will be utilized. Here, the dependent variable will be the incidence of myopia (or classification as a fast progressor), and the primary predictors will be the categorized durations of device usage and near work. The same set of covariates (age, gender, baseline refractive error, outdoor activity time) will be included to adjust for confounding. Odds ratios with corresponding 95% confidence intervals will be calculated to quantify the associations.

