#### Exploratory outcomes

*Time from randomization to occurrence of myopia (time-to-event outcome)*: The time from randomization to the occurrence of myopia will be measured as a time-to-event outcome. This endpoint will provide further insights into how quickly DIST delays the onset of myopia compared to the control group.*The association between near-work duration at home and myopia onset*: The duration of near-work activities (e.g., reading, using electronic devices) at home will be correlated with the onset of myopia to investigate environmental factors influencing myopia development. This data will help clarify the role of lifestyle factors in conjunction with DIST intervention.*The association between device usage duration and myopia onset*: The duration of DIST device usage will be correlated with the onset of myopia to explore potential dose–response relationships. This will determine whether longer usage of DIST is associated with a greater effect on myopia prevention, while controlling for other near work behaviors.*Changes in choroidal thickness (ChT) (µm) at 6 and 12 months follow-ups*: Changes in choroidal thickness will be monitored as an exploratory endpoint to assess the potential underlying physiological mechanisms of DIST technology in myopia prevention. Changes in choroidal thickness or blood flow as biomarkers of myopia progression are of significant importance in myopia prevention and control research.*Side effects and adverse events*: The occurrence of side effects and adverse events will be closely monitored throughout the study to ensure the safety of the DIST intervention. This will include any ocular or systemic issues reported by participants, and the severity of these events will be recorded.

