### Methods for additional analyses (e.g., subgroup analyses) {20b}

Subgroup analysis will be conducted based on the total duration of near work and the usage duration of devices in this study. The aim is to explore the impacts of these two factors on AL growth and the incidence rate of myopia among the subjects.

Firstly, we will divide the subjects into different subgroups according to specific criteria regarding the durations of near work and device usage.

Then, appropriate statistical methods will be employed for the analysis. To analyze the impact on the AL growth, which is a continuous variable, we will consider using analysis of variance (ANOVA) or regression analysis to compare the differences in AL changes among different subgroups and to determine whether there are significant associations between the durations of near work/device usage and the AL growth. In this process, relevant covariates such as age, gender, baseline refractive status, and outdoor activity time will be adjusted to control for potential confounding effects.

For the analysis of the impact on the incidence rate of myopia, which is a binary variable, logistic regression will be utilized. The myopia incidence will be set as the dependent variable, while the durations of near work and device usage will be the main independent variables. Additionally, the same set of covariates as mentioned above will be included in the model to account for confounding factors and to obtain more accurate estimates of the odds ratios and their corresponding confidence intervals, which can reflect the strength and significance of the associations between these factors and the myopia incidence.

Furthermore, interaction terms between the durations of near work and device usage might be considered in the models to explore whether there are combined effects of these two factors on the outcomes of interest. Through this comprehensive subgroup analysis, we expect to gain a more detailed and in-depth understanding of how the durations of near work and device usage influence the AL growth and the myopia incidence among the subjects.

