### Stratification and definition

Participants will be stratified into subgroups based on predetermined thresholds for both device usage and near work duration. For the purposes of this study, we will operationally define high-intensity near work behavior as a daily at-home near work duration of 2 h or more, while near work behavior lasting less than 2 h per day will be classified as low-intensity.

All participants will be included in the analysis. Adherence, defined as the ratio of actual device usage duration to planned usage duration, is calculated as both daily (daily adherence (%) = actual daily training duration/planned daily training duration × 100%) and overall (overall adherence (%) = ∑ (actual daily training duration)/∑ (planned daily training duration) × 100%). Subsequently, according to the adherence categories established by the Pediatric Eye Disease Investigator Group (PEDIG) [27, 28] (“excellent” (76%–100%), “good” (51%–75%), “fair” (26%–50%), and “poor” (0%–25%)), participants with an average daily device usage of 30 min or more will be classified as having high adherence, while those with less than 30 min per day will be classified as low adherence. These thresholds may be refined based on the statistical distribution of the relevant data at the end of the study.

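### The subgroup models cut device use and near work into two classes with movable cut points, although both are recorded as durations; the loss falls mainly on axial length, spherical equivalent and fast progressors

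*Protocol article*

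**What the plan says.** The exposure analyses appear in several places in the Protocol article.

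- **Methods for additional analyses {20b}.** First, "we will divide the subjects into different subgroups according to specific criteria regarding the durations of near work and device usage". For myopia incidence a logistic model follows in which "the durations of near work and device usage will be the main independent variables". For AL growth, either analysis of variance or regression may be used. An interaction between the two durations is optional.
- **Stratification and definition.** Near work is high-intensity at "a daily at-home near work duration of 2 h or more" and low-intensity below that. For the device, "participants with an average daily device usage of 30 min or more will be classified as having high adherence", and the rest are low. All participants are included. Then: "These thresholds may be refined based on the statistical distribution of the relevant data at the end of the study".
- **Continuous outcomes.** For AL and SE change, "the subgroup classifications (based on device usage and near work duration) will be the main independent variables".
- **Binary outcomes.** For myopia incidence and fast progression, "the primary predictors will be the categorized durations of device usage and near work".
- **Interaction analysis.** The interaction between the two durations is definite here.

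Both exposures are available in finer form. Device use is read weekly from backend records (section {11c}), and near work comes from log cards and questionnaires as daily averages (section {20a}). Section {20a} also plans an exploratory logistic model for onset on the durations, and a trend test on groups such as quartiles.

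**The concern.** Cutting a measured duration in two treats all children on one side of the cut as alike. A child at 31 min/day counts the same as one at 75, and near work of 2 h the same as 5 h. This costs precision on what the analysis is meant to show: under Rationale and interpretation, the results may inform how the device is best used, which is a question of dose.

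Three further problems follow.

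- The cuts can move once the data distribution is known, so the class results depend on a choice not yet fixed.
- A two-level near-work covariate leaves differences within each class unadjusted. Children who do more near work have more occasion to use the device, so part of any near-work effect can show up as a device effect.
- The text does not settle whether incidence is modelled on durations or classes, or whether the interaction is fitted.

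**Working it through.** **Figures in the plan.** The plan gives no power, distribution, split or correlation for these exposures, so there is no figure of its own to reproduce. Every exposure input below is an assumption. Group sizes come from the sample size section: 64 × 0.8 = 51.2, so about 51 completers per arm, 102 in the two device arms and 153 in all.

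**Step 1: information kept by a split.** For a normal exposure with a linear effect and a share q above the cut, the fraction kept is e = φ(z)² / [q(1 − q)], where z is the normal quantile at the cut. At q = 0.5, for example, 0.3989² / 0.25 = 0.637. If the continuous analysis has 80% power at two-sided 5%, the split has power Φ(2.80·√e − 1.96).

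| Split | Kept | Lost | Power |
|---|---|---|---|
| 50/50 | 0.637 | 36% | 61% |
| 40/60 | 0.622 | 38% | 60% |
| 30/70 | 0.576 | 42% | 57% |
| 20/80 | 0.490 | 51% | 50% |
| 10/90 | 0.342 | 66% | 37% |

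So 36% is the minimum for a normal exposure. It is not a general minimum: a uniform exposure cut at its median loses 25%.

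**Step 2: the plan's own cuts under a range of assumptions.** The loss is 1 minus the squared correlation between the exposure and its class indicator.

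- Near work cut at 2 h (mean 1.5–3 h, coefficient of variation 0.3–0.7; normal, gamma or lognormal): 36–76% lost.
- Device use cut at 30 min, device arms only (mean 30–60 min, SD 10–30): 32–99% lost. The top of the range arises when nearly all children are close to the planned 1 h, so almost none fall below the cut.
- Device use cut at 30 min, with controls at 0 min included: 8–39% lost. The smaller loss says little about dose, because the cut then mostly separates control from device arms.

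**Step 3: near-work confounding left in the device effect.** With bivariate normal exposures, usage/near-work correlation 0.2–0.5 and splits from 50/50 to 20/80, adjusting for two-class near work leaves about 37–58% of the confounding.

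**Step 4: consequence for an inert device.** Assumptions: usage mean 45, SD 20 min; 60% above the near-work cut; AL-growth SD 0.2 mm; 4,000 simulated data sets per scenario. The correlation pairs are usage/near work, then near work/AL growth. Both exposures are entered as classes.

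| Correlations | Device arms only (n = 102) | All participants (n = 153) |
|---|---|---|
| 0.3 / 0.2 | about 5% false positives | about 5% |
| 0.5 / 0.3 | about 6%; bias 0.019 mm toward harm | about 6%; bias 0.008 mm |
| 0.7 / 0.4 | about 10%; bias 0.035 mm | about 7%; bias 0.015 mm |

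Repeat runs at the strongest correlations reached nearly 12% and 8%. With both durations continuous, the rate was about 5% with no bias. That held within the device arms, and with all participants plus an arm term.

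**Step 5: which outcomes are exposed.**

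- Onset has the duration-based model in {20a}, besides the class-based one.
- AL has the class-based model, plus an open choice of method in {20b}.
- SE change and fast progressors have the class-based models only.

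**The case against.** Three arguments on the other side carry weight.

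- **The text may not hold two rival incidence models.** A reader might infer a flat contradiction between {20b} and the later section. But {20b} itself begins by dividing children into subgroups, and what follows can be read as the detail of that plan. This stands: the exposure form is ambiguous rather than stated in two incompatible ways.
- **The aim of isolating device use is met elsewhere for onset.** Under Exploratory outcomes, device use is to be related to onset "while controlling for other near work behaviors". A reader might infer that the classes defeat this aim. They do not: the model planned for it in {20a} uses durations for both exposures. This also stands, and confines the concern mainly to AL, SE and fast progressors.
- **Subgroup results need classes, and the analysis is supplementary.** The plan says this work complements the main findings, and high/low groups are easy to communicate. If the true effect were a step at the cut, classes would also be the better model. This supports keeping the classes for display. It does not support making them the only model for SE change and fast progression, least of all with cuts that may move.

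**Conclusion.** The point holds as a weakness of supplementary analyses. With a roughly normal exposure and a linear effect, the two-class form loses at least 36% of the exposure information, taking 80% power to about 61% or lower. For device use with controls included, the loss is smaller (8–39% in the scenarios tried), but the contrast then mixes dose with allocation.

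Two stronger readings are not supported. A single loss of 40–50% cannot be derived from the documents; it needs a normal exposure and a split of about 35/65 to 20/80. Nor can it be said that an inert device would look harmful. The false-positive rate is about 5–7% with all participants, the planned analysis set, and about 5–10% in the device arms alone. It is slightly higher in repeat runs at the strongest assumed correlations and nominal at weak ones. Residual confounding is therefore a conditional, secondary reason for the change. The information loss and the movable cuts are the main ones.

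The primary comparison of arms and the sample size do not depend on any of this.

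**What to change.** In {20b} and in the sections on continuous outcomes, binary outcomes and interaction:

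- Enter device minutes/day and near-work hours/day as continuous variables, with linearity checked (for example by a restricted cubic spline), as the lead exposure analysis for AL change, SE change, fast progression and incidence.
- Estimate the device-minutes effect within the two device arms, or in all participants with a term for arm, so that dose is not mixed with allocation.
- State once whether the interaction between the durations is included.
- Keep the 30 min and 2 h classes for descriptive subgroup tables.

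This changes wording only; no new data are needed. The cost is that a per-unit coefficient is less immediate to read than high versus low, which the descriptive tables offset. Recruitment is reported as completed in September 2025, so the last 12-month visits fall around September 2026. The protocol version is dated March 2026, so at that date the form could still be fixed before final data.

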#### Interaction analysis

Interaction terms between device usage duration and near work duration will be incorporated into the regression models to explore potential synergistic effects on myopia prevention outcomes.

#### Rationale and interpretation

The independent analysis of these subgroups is designed to provide a deeper understanding of how both device usage and near work independently and jointly influence myopia progression indicators. This analysis is not dependent on the primary endpoint results; rather, it is intended to complement the overall findings and help refine targeted intervention strategies for high-risk pre-myopic children.

The results will be presented as adjusted means (for continuous outcomes) and adjusted odds ratios (for binary outcomes) along with their standard errors or 95% confidence intervals. This comprehensive subgroup analysis will yield insights that may inform future recommendations for reducing near work-related visual stress and optimizing the use of the DIST device in myopia prevention.

### Methods in analysis to handle protocol non-adherence and any statistical methods to handle missing data {20c}

To comprehensively assess the impact of the devices on delaying myopia onset, we will conduct data analyses using both the Intention-to-Treat (ITT) analysis as the primary result and the Per-Protocol (PP) analysis as the secondary result, along with appropriate handling of missing data in both processes.

#### ITT analysis (primary result)

The ITT analysis will be carried out to reflect the real-world application effect of the devices in preventing myopia onset. In case a participant drops out or has missing data during the follow-up period, we will use the Last Observation Carried Forward (LOCF) method. This ensures that all randomly assigned participants are retained in the analysis, maintaining the integrity of the randomization and providing a comprehensive view of the overall effect of the devices in a real-life scenario.

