### Outcomes {12}

#### Primary outcome

##### Proportion of myopia onset

Myopia onset is defined as cycloplegic spherical equivalent refractive error of at least − 0.50D in either eye over 1 year, in accordance with the Refractive Error Study in Children. This outcome assesses the effectiveness of the DIST intervention in delaying the onset of myopia in pre-myopic children.

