### Plans to promote participant retention and complete follow-up {18b}

To ensure high participant retention and complete follow-up throughout the study, a comprehensive strategy will be implemented. This strategy will focus on maintaining participant engagement, minimizing dropout rates, and addressing potential challenges that may arise during the study.

Engagement and retention strategies
Regular communication: Participants will be regularly contacted via phone calls, text messages, or mobile applications to provide reminders of upcoming appointments and to maintain engagement.Flexible scheduling: Follow-up visits will be scheduled at times convenient for the participants and their families, such as weekends and holidays.Incentives: To further encourage retention, participants will receive small incentives, such as gift cards or study-related materials, upon completion of key milestones (e.g., baseline, 6-month, and 12-month visits).

2.Handling withdrawals or treatment modifications

In the event that a participant decides to withdraw or is unable to complete the study, their outcome data up to the point of withdrawal will be collected. This ensures that even if they do not complete the entire study, the data they have contributed remains valuable.Reasons for withdrawal: Participants who withdraw will be asked to provide the reason for their decision (e.g., personal, logistical, or health-related issues), which will be documented for further analysis and to inform potential improvements in future studies.Changes in treatment plan: If participants need to switch to an alternative treatment, the research team will collect relevant outcome data before the change is made, ensuring that the participant’s previous data remains part of the analysis. This will allow the study to account for the impact of treatment changes on the outcomes.

3.Follow-up and data collection

In the event of missing data or uncompleted follow-up visits, efforts will be made to contact participants to reschedule and collect the necessary data. If a participant cannot be reached for any follow-up visit, the last available data will be included in the analysis, and the participant will be considered as missing for subsequent follow-up points.

By employing these strategies, we aim to minimize participant dropout, ensure high-quality follow-up data, and maximize the retention of participants throughout the 1-year study period.

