## Statistical methods

### Statistical methods for primary and secondary outcomes {20a}

Analysis of primary outcomeIn this participant-based study, the primary outcome is the proportion of myopia onset. This outcome is measured as a binary (nominal) variable. Participants are classified as either having experienced the onset of myopia (Yes) or not (No), based on whether their cycloplegic spherical equivalent refractive error reaches or exceeds − 0.50 D in either eye at the 1-year follow-up. This is a single endpoint measure, assessed once at the end of the 1-year follow-up period. It provides a proportion of participants who experience the onset of myopia. To test the effectiveness of DIST on the primary outcomes, logistic regression including trend analysis will be used, which can both examine the overall relationship and detect potential trends related to different treatments. In addition, covariates such as baseline spherical equivalent refractive error, age, gender, and study group (Intervention vs. Control) will be included to ensure a parsimonious logistic regression model while controlling for factors known to influence myopia onset and progression.The primary analysis will be conducted on the ITT population, which is defined as all randomized participants with at least one post-baseline measurement. For all analyses, the underlying model assumptions will be rigorously evaluated. For instance, when applying logistic regression to assess the binary primary outcome, we will verify the linearity of the logit for continuous covariates using methods such as the Box–Tidwell test, assess multicollinearity via variance inflation factors (VIF), and examine residuals and influence statistics (e.g., Cook’s distance) to identify any influential outliers. Missing data will be addressed using multiple imputations by chained equations under the assumption of data missing at random (MAR), with sensitivity analyses planned to assess the impact of outliers, nonadherence, and loss to follow-up.Analysis of secondary outcomesThe secondary outcomes are intended to capture aspects of the intervention effect that are not fully reflected by the primary outcome. For example, even if the primary outcome (myopia onset) does not show a statistically significant difference, significant changes in spherical equivalent or axial length may still be observed, thereby indicating a potential benefit of the intervention in slowing myopia progression.For the three secondary outcomes: (1) the proportion of fast progressors over 1 year, (2) changes in spherical equivalent progression, and (3) changes in AL (mm) at each follow-up point, the following statistical procedures will be employed:Proportion of fast progressors (binary outcome)This endpoint will be analyzed using logistic regression. The model will estimate the odds of being classified as a fast progressor over 1 year, comparing the intervention group to the control group. Covariates to be included in the model are baseline spherical equivalent refractive error (continuous), age (continuous), and gender (categorical), as these factors have been shown in prior research to influence myopia progression. The study group (intervention vs. control) will be the primary factor of interest. These covariates are selected based on their theoretical relevance and empirical support, ensuring a parsimonious model that controls for potential confounding without overfitting.Changes in spherical equivalent progression (continuous outcome)The change in spherical equivalent progression over time will be analyzed using a repeated measures mixed-effects model. This model will account for within-subject correlations across multiple follow-up points and will include fixed effects for the treatment group, time (as a categorical or continuous variable depending on the observed pattern), and the interaction between treatment and time. Baseline spherical equivalent refractive error, age, and gender will be included as covariates to adjust for initial differences and known predictors of refractive change. The rationale for these covariates is their established association with myopia progression, ensuring that the model is both explanatory and parsimonious. Model selection procedures, such as stepwise backward elimination based on the Akaike Information Criterion (AIC) or likelihood ratio tests, will be applied to refine the final model.Changes in AL (mm)Similar to the spherical equivalent endpoint, changes in axial length (measured in mm) at each follow-up will be analyzed using a repeated measures mixed-effects model or an analysis of covariance (ANCOVA) for longitudinal data. The model will include fixed effects for treatment, time, and their interaction. Covariates will include baseline axial length, baseline spherical equivalent, age, and gender. These factors are chosen because they are known to influence ocular growth and, consequently, axial elongation. As with the other endpoints, a parsimonious model will be achieved by using stepwise selection methods or likelihood ratio tests to retain only covariates that contribute significantly to explaining the variation in axial length change.The results of these analyses will be presented as adjusted odds ratios with 95% confidence intervals for the binary outcome and as least-squares means (LSMEANS) with standard errors for the continuous outcomes. In addition, p-values will be reported to assess the statistical significance of the observed differences between intervention groups.Analysis of exploratory outcomesTime-to-myopia onset analysisFor comparing the time to myopia onset (time-to-event outcome) among 3 treatment groups, we all create a number-at-risk table and use the Kaplan–Meier method to estimate survival curves, followed by the log-rank test to assess differences statistically.Myopia onset associationsA logistic regression model will be built with myopia onset as the dependent variable and near-work duration, device usage duration, and confounding factors as independent variables. The near-work duration was derived from the near-work log cards and questionnaires, with the daily averages taken for analysis. Odds ratio (OR) and its 95% confidence interval will be estimated to determine associations while controlling for confounding.Dose–response relationship analysisWe will group near work and device usage durations (e.g., by quartiles). Use the Cochrance–Armitage trend test to analyze if there’s a dose–response relationship. Curve fitting (such as polynomial regression) can also be used to further explore the non-linear relationship between them.Choroidal thickness changesFor exploring changes in choroidal thickness during different follow-up periods among three groups, repeated measures analysis of variance (ANOVA) will be used. If significant effects are found, post hoc tests (like Bonferroni or Tukey’s) will determine specific differences.

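### The primary ITT analysis carries two conflicting missing-data rules, and one of them, LOCF, can only score a child lost before month 6 as not myopic

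*Protocol article*

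**What the plan says.** Section {20c} names the "Intention-to-Treat (ITT) analysis as the primary result". Two places then say how missing outcomes are handled in that analysis.

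- Section {20a}, in the paragraph on the primary outcome: "Missing data will be addressed using multiple imputations by chained equations under the assumption of data missing at random (MAR"), followed by sensitivity analyses for outliers, nonadherence and loss to follow-up.
- The ITT analysis (primary result) section under {20c}: "In case a participant drops out or has missing data during the follow-up period, we will use the Last Observation Carried Forward (LOCF) method".

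The analysis set is also described twice.

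- Section {20a}: "The primary analysis will be conducted on the ITT population, which is defined as all randomized participants with at least one post-baseline measurement".
- ITT analysis (primary result), speaking of LOCF: "This ensures that all randomly assigned participants are retained in the analysis".

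Section {18b} adds that, for a child who cannot be reached, "the last available data will be included in the analysis, and the participant will be considered as missing for subsequent follow-up points".

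The endpoint rests on cycloplegia: "Myopia onset is defined as cycloplegic spherical equivalent refractive error of at least" −0.50 D in either eye. Eligibility requires a cycloplegic SE above −0.50 D at entry. Table 1 and section {18a} place cycloplegic refraction at baseline, 6 months and 12 months. The 3-month visit has refraction without cycloplegia only.

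**The concern.** One primary analysis cannot follow both rules. With both in print, the choice could be made after the data are seen, and whichever is chosen contradicts a published section.

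The rules are not interchangeable for this endpoint. Every child starts as a non-case and can only become one. Carrying an early value forward therefore does not give a neutral guess; it fixes the answer at no myopia and treats that as observed. Each arm's estimated onset then depends on how many of its children were lost and when, as well as on the treatment. Families are not blinded, and only the device arms have a minimum daily use and weekly usage checks, so equal loss across arms cannot be taken for granted.

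**Working it through.** **Inputs from the article:** onset 54% (control) and 21% (intervention); α = 0.025/2 = 0.0125; power 80%; superiority margin 0.05 in the sample-size section; dropout 20%; 64 per group.

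**Assumptions:** the split of loss between arms and its timing, which the article does not give; loss unrelated to onset; both eyes above −0.50 D at baseline; α = 0.0125 read as one-sided, because that reading reproduces the sample size.

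**Step 1. The plan's own figure.** n = [0.54×0.46 + 0.21×0.79] × (2.2414 + 0.8416)² / (0.33 − 0.05)² = 0.4143 × 9.505 / 0.0784 = 50.2. This rounds up to 51, and 51/0.8 = 63.75, so 64 per group. The sample size reproduces and is not in dispute.

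**Step 2. What LOCF has to carry.**

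| Last visit attended | Last cycloplegic value | LOCF result |
|---|---|---|
| Baseline | Baseline, above −0.50 D | No myopia (child is outside the {20a} set) |
| 3 months | Baseline, above −0.50 D | No myopia |
| 6 months | 6 months | Onset in months 6–12 missed |

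For losses before month 6, recorded rate = true rate × (1 − share lost).

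**Step 3. Equal 20% loss before month 6, all randomised children analysed.** Control 0.54 × 0.80 = 43.2%; intervention 0.21 × 0.80 = 16.8%. The difference falls from 33 to 26.4 points.

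**Step 4. Unequal loss, true onset 54% in both arms.** Use a zero-difference test, since section {20a} states no margin for the analysis. Error = P(Z > 2.2414 − bias/SE), with SE from two binomials.

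- *All loss before month 6, all randomised analysed, 20% device vs 5% control:* 0.54 × 0.80 = 43.2% vs 0.54 × 0.95 = 51.3%. Bias 8.1 points, SE 0.0880, ratio 0.921, error 9.3%.
- *Same setting, 20% vs 10%:* 43.2% vs 48.6%. Bias 5.4 points, error 5.2%.
- *Half of the losses after month 6, with half of their events already seen:* the share of events missed is 0.75 × loss. For 20% vs 5%: 45.9% vs 52.0%, bias 6.1 points, error 6.0%. For 20% vs 10%: error 3.7%.
- *Set of section {20a}, half of the losses having no post-baseline visit and so excluded, the rest seen at 3 months only, 20% vs 5%:* 0.54 × 0.80/0.90 = 48.0% vs 0.54 × 0.95/0.975 = 52.6%. Bias 4.6 points, error 4.1%.
- *Reverse split, 5% device vs 20% control, all before month 6, all randomised:* bias −8.1 points. The false-positive rate falls to about 0.1%, and a real benefit would be understated.

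**The case against.** Several stronger readings are tempting, and the article does not support them.

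- **A third conflicting rule in section {18b}.** A reader might infer that it both carries data forward and treats the child as missing. It can equally mean that observed data are kept and later visits left missing, which agrees with section {20a}. It is ambiguous rather than contradictory.
- **Two rival ITT definitions.** Only section {20a} defines the set ("ITT population, which is defined as all randomized participants with at least one post-baseline measurement"). The other sentence describes what LOCF is claimed to achieve. The two still disagree about any child with no post-baseline measurement, so the wording must be aligned.
- **Every early loss becomes a non-event.** That holds if all randomised children are analysed. Under the {20a} set it holds for those seen at 3 months but not at 6. The article does not say how the non-cycloplegic 3-month refraction would be treated, but the endpoint definition does not accept it.
- **The trial's error rate is 9.3%.** That figure needs all loss before month 6, the all-randomised set, a fourfold imbalance and heavier loss in the device arm. Only the overall 20% is documented. Applying the 0.05 margin to the test would cut it to 2.9%; a two-sided reading of 0.0125 would give 5.7% in the favourable tail. The planned model is also covariate-adjusted logistic regression, which the simple test only approximates.
- **The bias favours the device.** Section {11b} keeps children who stop the device in the study unless they ask to withdraw, so the burden of use need not become missing outcomes. Heavier loss in control reverses the bias.
- **A child seen only at 3 months should not be in the ITT set.** Under imputation this is ordinary missing data.
- **No sensitivity analysis is planned.** Section {20a} plans one for loss to follow-up.

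What remains untouched is the direct conflict between the two rules and the mechanism by which LOCF forces non-events. Neither is detail left to an analysis plan: the article states both rules for its primary result.

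**Conclusion.** The point holds and must be fixed. The primary ITT analysis has two incompatible missing-data rules and inconsistent wording of its population, and LOCF is unsuitable for an onset endpoint measured under cycloplegia only at 6 and 12 months.

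The size depends on dropout. At the protocol's own 20%, if all of it falls before month 6, is equal across arms and all randomised children are analysed, the planned effect shrinks by a fifth, from 33 to 26.4 points. With 20% device versus 5% control loss and no true effect, the false benefit is 4.6 to 8.1 points and the one-sided error about 4% to 9% against a nominal 1.25%. The reverse split biases against the device. The splits and timings are illustrations. The conclusion that the estimate depends on dropout does not rest on any one of them.

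**What to change.** 1. Remove LOCF as the primary rule from the ITT analysis section. Keep the chained-equations imputation of section {20a} as the single primary method, imputing cycloplegic SE and deriving myopia from the imputed values.
2. Define ITT once, as all randomised children in their allocated arm, and use that definition in {20a} and {20c}.
3. Reword section {18b} to say that observed data are kept and later visits are treated as missing, with no value carried forward.
4. Have the loss-to-follow-up sensitivity analysis already planned in {20a} include a missing-not-at-random scenario, for example a delta adjustment. The imputation model's predictors can be left to the analysis plan.

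The cost is wording and modest programming; no visit, measurement or sample-size change is needed. The article gives September 2025 as the end of recruitment, so 12-month visits for the last children fall around September 2026. The rule should be fixed before outcome data are examined by arm.
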